#### Secondary outcome measures

The secondary outcome measures will be:Changes in immune indicators (detected by flow cytometry).Changes in inflammation indicators (detected by enzyme-linked immunosorbent assay).Respiratory support: the duration of oxygen therapy, high-flow humidification oxygen therapy, noninvasive mechanical ventilation, and invasive mechanical ventilation.Mortality rate after 28 days.Blood gas analysis (including blood lactate).Improvement in acute physiology and chronic health evaluation II (APACHE II) scores; the evaluation of improvement is based on differences in the APACHE II scores before and after the intervention.Improvement in clinical symptoms based on improvement in dyspnea, cough, sputum, and the use of accessory respiratory muscles (using the scoring system shown in Table 2). According to the differences in the scores before and after the intervention, the evaluation criteria are as follows:Significantly effective: the score decreased ≥ 3;Effective: the score decreased from 1 to 3;Ineffective: no change in the score;Exacerbation: the score increased ≥ 1;Name, dosage, and duration of antibiotic use.Name, dosage, and duration of corticosteroid use.Changes in laboratory inspection indicators.Incidence of complications.Length and cost of intensive care unit (ICU) stay.Length and cost of hospitalization.

**Table 2 Tab2:** The clinical symptoms scoring system of AECOPD

Score	Dyspnea	Cough	Sputum production	Use of accessory respiratory muscles
0	–	No cough	No sputum	No neck muscle tension and periodic contraction
1	Shortness of breath when flat on the ground or walking up one floor level	Intermittent cough, but no symptoms at night	Sputum volume ≤ 30 mL the whole day and night	Neck muscle tension, but no obvious muscle activity
2	Shortness of breath when walking with peers	Sometimes cough, which probably affects sleep	Sputum volume ≥ 30 mL and ≤ 50 mL	Visible slight contraction of the neck muscles
3	Need to stop so as to breathe when walking at their own speed	Frequent cough affecting sleep	Sputum volume ≥ 50 mL and ≤ 100 mL	Moderate contraction of the neck muscles, not with clavicular fossa and intercostal retraction
4	Shortness of breath when dressing or undressing	–	Sputum volume ≥ 100 mL	Strong contraction of the neck muscles, with abdominal contradictory movement

The evaluation criteria for the improvement in clinical symptoms is according to the total scores of the 4 items

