### Statistical analysis

An independent professional statistician and researcher will develop a complete statistical analysis plan for the trial, prior to the final analysis. The statistical analysis will be performed by the statistician in a blinded manner using the Statistical Analysis System (SAS) software version 9.2. The main analysis will be based on the full analysis set (FAS). According to the intention-to-treat principle, the FAS refers to a set of data on any participants who randomly receive at least one treatment. The per-protocol set (PPS), a subset of the FAS, includes data on only those participants who completed the trial without any violations of or deviations from the protocol. The FAS and PPS will be used for the assessment of efficacy. For the safety assessment, the safety set (SS) will be used, which includes patients who have received at least one safety evaluation after treatment.

All data, including the number of subjects included, drop-outs, elimination conditions, demographics, baseline characteristics, and efficacy and safety assessment, will be analyzed using different approaches. Descriptive and univariate statistics will be used to characterize the study participants and compare the baseline characteristics between the two groups. The primary outcome is the rate of endotracheal intubation, which will be determined by the Cochran-Mantel-Haenszel (CMH) test in the FAS population. We prefer to use the CMH chi-square test because it can deal with confounders of multi-center effects. Two-sided tests will be performed for all the other statistical analyses. The CMH chi-squared test or Fisher’s exact test will be used for comparing the categorical outcomes. The continuous outcomes will be analyzed by Student’s *t* test, while the AEs will be presented using descriptive statistics and compared using a chi-square test. A *P* value <0.05 will be considered to indicate statistical significance. Missing data will be explored and adjusted using the imputation method.

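### The ordered four-class symptom outcome may be compared by Fisher's exact test or an unspecified CMH chi-square; Fisher's test ignores the class order and drops the centre strata

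*Protocol article*

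**What the plan says.** In the protocol article, Secondary outcome measures sums four symptom items ("The evaluation criteria for the improvement in clinical symptoms is according to the total scores of the 4 items") and classifies the change from before to after the intervention:

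- "Significantly effective: the score decreased ≥ 3"
- "Effective: the score decreased from 1 to 3"
- "Ineffective: no change in the score;Exacerbation: the score increased ≥ 1"

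These classes run from best to worst. (A fall of exactly 3 fits both of the top two; that is a separate point and does not matter here.)

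Statistical analysis names two tests for categorical outcomes in general: a CMH chi-square, or Fisher's "exact test will be used for comparing the categorical outcomes". It does not say which CMH statistic is meant or when Fisher's test replaces CMH, and it makes no separate provision for ordered outcomes. Its preference for CMH, stated for the primary outcome, rests on centre effects: "We prefer to use the CMH chi-square test because it can deal with confounders of multi-center effects". Continuous outcomes go to a t test ("The continuous outcomes will be analyzed by Student"). A full statistical analysis plan is announced and is not available here.

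**The concern.** The question about an ordered outcome is whether patients on Xuebijing tend to fall in better classes than patients on placebo. A test that treats the four classes as unordered labels answers a wider question: do the two distributions differ in any pattern? Two things follow.

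- **Power.** Three degrees of freedom are spent where one would do, so a consistent shift towards better classes is easier to miss.
- **Meaning.** The test can be significant when one arm has more patients in some better classes and also more in some worse ones. P < 0.05 on an outcome labelled improvement would then not mean improvement.

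Fisher's test adds a third loss. Applied to the pooled table, it gives up the adjustment for centre that the same section argues for.

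**Working it through.** **The plan's own figure.** The Sample size section gives 127 per group for intubation rates of 15.2% and 4.7%, two-sided alpha 0.05 and 80% power. The pooled-variance formula without continuity correction gives 126.4, so 127; then 127/0.85 = 149.4, so 150. Both figures reproduce. No power, class distribution or effect size is given for the symptom outcome, so everything below on power rests on assumptions.

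**Step 1: cost of the extra degrees of freedom.** Give a 1-df and a 3-df chi-square the same noncentrality λ = (1.96 + z_power)². For 80% power on 1 df, λ = 7.85; the 3-df test then has 64% power. At 50% the 3-df test has 35%, at 90% it has 78%, and at 95% it has 87%. The loss is 14 to 17 points when the ordered test has 50 to 85% power, and shrinks above that.

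**Step 2: simulation.** Assumptions: proportional-odds shift; unordered 3-df chi-square against the ordered 1-df rank-score statistic; unstratified; 20,000 runs. With an assumed control split of 40/35/15/10% (best to worst) and 150 per arm:

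| Odds ratio | Unordered | Ordered | Loss (points) |
|---|---|---|---|
| 1.5 | 32% | 47% | 15 |
| 1.8 | 61% | 78% | 17 |
| 2.0 | 76% | 89% | 13 |
| 2.5 | 95% | 99% | 4 |

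- Five assumed control splits, at 127 and 150 per arm: losses of about 12 to 18 points at odds ratios 1.5 to 1.8, 11 to 18 at 2.0, and 2 to 11 at 2.5.
- Stratified over nine centres, 35/40/15/10%, 127 per arm: 25% against 40% at 1.5, 52% against 70% at 1.8, and 67% against 83% at 2.0. A repeat of this setting gave losses of 13 to 19 points over odds ratios 1.5 to 2.0 and 4 to 7 at 2.5. Both tests held size near 5%.
- Exact two-by-four Fisher test in place of the chi-square, 40/35/15/10%, 1,500 runs: losses of 15, 15 and 13 points at 1.5, 1.8 and 2.0 with 150 per arm. One run at 127 per arm and odds ratio 1.8 gave 20, but with so few runs that is uncertain by two or three points.

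**Step 3: a shift that the unordered test misses.** Illustrative counts, 127 per arm: 62/46/12/7 against 45/51/19/12. The first arm is better throughout. Unordered chi-square 5.86 on 3 df, P = 0.12; rank-score statistic 5.80 on 1 df, P = 0.016.

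**Step 4: significance with no net shift.** Illustrative counts, 150 per arm: 45/60/30/15 against 60/30/45/15. Scoring the classes 0 to 3, the means are (60 + 60 + 45)/150 = 1.1 and (30 + 90 + 45)/150 = 1.1, which are identical.

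- Unordered: expected counts per arm are 52.5, 45, 37.5 and 15. Chi-square = 2 × (7.5²/52.5 + 15²/45 + 7.5²/37.5 + 0) = 2 × (1.07 + 5.00 + 1.50) = 15.14 on 3 df, P = 0.0017. Exact Fisher gives P = 0.0016.
- Ordered: the midranks are 53, 150.5, 233 and 285.5, with mean 150.5. The first arm's rank-sum deviation is 45 × (−97.5) + 60 × 0 + 30 × 82.5 + 15 × 135 = 112.5. Its variance is about 515,562. The statistic is 112.5²/515,562 = 0.025, P = 0.88.

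If the true class probabilities matched these two arms, the unordered test would be significant about 93% of the time and the ordered test about 5%.

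**The case against.** A reader might infer that the plan commits this outcome to an unordered test. It does not. The CMH family includes the row-mean-scores statistic, so the wording already permits an ordered analysis. Which CMH statistic serves which secondary outcome is ordinary content for the analysis plan that is not shown. No test is named for this outcome specifically, and the score change could instead be treated as continuous and go to the t test. Fisher's test is conventionally a fallback for sparse tables, and the table need not be sparse: in the step 3 example the smallest expected count is 9.5. All of this stands, and it confines the point. What remains is that Fisher's test is named as an open alternative for every categorical outcome with no condition on its use, and no later detail can make that test use order on a two-by-four table.

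A reader might also take a loss of around 15 points as a property of this trial. The documents do not support that either. The proportional-odds assumption favours the ordered test, and the loss depends on effect size. With 35/40/15/10% and 150 per arm it is 4 points at an odds ratio of 1.2, 9 at 1.3, and about 3 at 2.5.

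Finally, both tests are valid, and the ordered one has a blind spot. With illustrative counts of 60/33/14/20 against 45/55/20/7, exacerbations are 20 against 7. The unordered test gives P = 0.002 and the ordered test P = 0.57. That is a real trade-off, and the reason to report the class counts as well.

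**Conclusion.** The point holds in a limited form. The article defines an ordered outcome and leaves open a test that discards the order and the centre strata, beside a CMH test whose form is unstated. If Fisher's test or the general-association CMH is used, the loss is roughly 11 to 19 power points at odds ratios of 1.5 to 2.0 and about 2 to 11 at 2.5. Those figures depend on assumed class distributions, a proportional-odds shift and 127 to 150 patients per arm. If the row-mean-scores CMH is used, there is no such loss. That an unordered test can be significant without net improvement needs no assumed effect size; the counts in step 4 show it. The outcome is one of 13 listed secondary measures, and the binary primary comparison is unaffected, so this is a worthwhile refinement and not a serious flaw.

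**What to change.** In Statistical analysis, or in the analysis plan before unblinding:

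- For the four symptom-response classes, name the CMH row-mean-scores statistic stratified by centre, with modified ridit scores (the van Elteren test).
- Restrict Fisher's exact test to sparse binary or unordered outcomes.
- Report the four class counts by arm, so that an excess of exacerbations stays visible whatever the test says.

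The cost is a sentence or two. The statistic is standard CMH output in the software the article names, and it keeps the sponsor's preferred test family and centre adjustment. It also removes a choice between tests that could otherwise be made after seeing the data. The downside is less sensitivity to differences that are not a shift, which the class counts partly offset.

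### Continuous outcomes, including before-after changes, are compared by Student's t test with no adjustment for baseline or centre; ANCOVA would be more precise at no cost in data

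*Protocol article*

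**What the plan says.** The Statistical analysis section of the protocol article gives one method for this class of outcome: "The continuous outcomes will be analyzed by" Student's t test. No covariate is named.

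The Secondary outcome measures section makes several of these outcomes before-after changes. For APACHE II, "the evaluation of improvement is based on differences in the APACHE II scores before and after the intervention". Two further entries are "Changes in immune indicators (detected by flow cytometry" and "Changes in inflammation indicators (detected by enzyme-linked immunosorbent assay", each with the assay in brackets. Blood gases are listed differently, as "Blood gas analysis (including blood lactate", without saying whether the level or the change is compared.

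In the analysis text, baseline data serve only to describe the participants and to "compare the baseline characteristics between the two groups". For the primary outcome the reason for the test is given: "We prefer to use the CMH chi-square test because it can deal with confounders of multi-center effects". The same family of test is offered for categorical outcomes. The t test has no counterpart to it.

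A statistician and researcher "will develop a complete statistical analysis plan for the trial, prior to the final analysis". That plan is not available here.

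**The concern.** A t test on change scores fixes the coefficient of baseline at exactly 1. When follow-up correlates imperfectly with baseline, that subtracts too much: it adds baseline noise to the outcome, and a group that starts higher by chance tends to show the larger fall whatever its treatment. ANCOVA estimates the coefficient from the data and avoids both problems.

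Centre raises a question of consistency. The article regards centre effects as important enough to decide the primary test, but continuous outcomes from the same centres (nine in Table 1) are pooled without a centre term. The Randomization section describes no stratification by centre or severity, so nothing stated there limits chance imbalance in these variables.

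The stakes are higher than usual for secondary outcomes. The Objectives section lists the effect on regulatory T lymphocytes as the second primary objective. The intubation rate cannot answer it; the immune indicators are the listed outcomes that can.

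**Working it through.** **The plan's own figure.** The only design calculation is for the primary outcome (Sample size section): 15.2% against 4.7%, two-sided alpha 0.05, beta 0.2. With the pooled-variance formula, n = [1.96 × √(2 × 0.0995 × 0.9005) + 0.8416 × √(0.152 × 0.848 + 0.047 × 0.953)]² / 0.105² = 126.4, so 127 per group. Then 127 / 0.85 = 149.4, so 150. Both stated figures reproduce. No continuous outcome has a stated power, standard deviation (SD) or correlation.

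**Assumptions for the comparison.** SD s, equal at baseline and follow-up; correlation rho between the two, taken from 0.3 to 0.8. Neither is in the article. All 150 per group are taken as measured.

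**Variance per patient.**
- Change score: s² + s² − 2·rho·s² = 2(1 − rho)s²
- ANCOVA residual: (1 − rho²)s²
- ANCOVA relative to change: (1 − rho²) / [2(1 − rho)] = (1 + rho)/2

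**Power.** Take the difference that the change-score test detects with 80% power at 150 per group. ANCOVA power is then Φ[(1.96 + 0.8416) × √(2/(1 + rho)) − 1.96]. The number per group that ANCOVA needs for 80% power is 150 × (1 + rho)/2.

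| rho | change variance (s²) | ANCOVA variance (s²) | ANCOVA/change | change/ANCOVA | ANCOVA power | ANCOVA n per group |
|---|---|---|---|---|---|---|
| 0.3 | 1.40 | 0.91 | 0.65 | 1.54 | 93.5% | 98 |
| 0.5 | 1.00 | 0.75 | 0.75 | 1.33 | 89.9% | 113 |
| 0.7 | 0.60 | 0.51 | 0.85 | 1.18 | 86.0% | 128 |
| 0.8 | 0.40 | 0.36 | 0.90 | 1.11 | 84.0% | 135 |

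The ratio is below 1 for every rho below 1, so the direction does not depend on the value assumed; only the size does.

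**Chance imbalance.** If the treatment group starts 0.2 SD higher, the change-score contrast shifts by −(1 − rho) × 0.2: −0.14, −0.10 and −0.06 SD at rho 0.3, 0.5 and 0.7. If follow-up levels are compared instead, the shift is rho × 0.2: +0.06, +0.10 and +0.14 SD. ANCOVA removes it in either case.

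An imbalance of 0.2 SD is on the large side. The standard error of the baseline difference is √(2/150) = 0.115 SD, so 0.2 SD is 1.73 standard errors, expected in about 8% of such trials for any one variable. The average absolute imbalance is about 0.09 SD; at rho 0.5 that shifts the contrast by about 0.05 SD.

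**Centre.** The gain from a centre term cannot be sized, because the article gives no between-centre variance for any continuous outcome.

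**The case against.** The strongest reply is that nothing here is an error. In a randomized trial a two-sample t test on change scores is unbiased on average and keeps its type I error. The Randomization section describes no stratification by centre, so leaving centre out does not invalidate the test. Covariates are often settled in the statistical analysis plan, which the article promises, and no continuous outcome has a power target that is being missed. The correlation is assumed, and at 0.8 the variance excess is only 11%. All of this stands, and it limits the point to one about efficiency.

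It does not remove the point. The article does not leave the method open; it names the t test, and an analysis plan that follows the article would carry it forward.

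A reader might infer more than the article supports:
- **That baseline values are thrown away.** A change score subtracts baseline. What is missing is its use as a covariate. Baseline would be ignored only where follow-up levels are compared.
- **That blood gases are a change outcome.** The article does not say so, and the variance ratio above would not apply to levels.
- **That the treatment comparison is biased.** The shifts above arise only given a chance imbalance, and the typical one is small.
- **That log transformation, a day-6 endpoint or a repeated-measures model is needed.** The text says nothing about skewness, and which outcome is measured when is in Figure 2, which is not shown here.

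**Conclusion.** The point holds as a free improvement. The article fixes an unadjusted t test for continuous outcomes, although several of them are before-after changes and although its own reasoning for the primary test treats centre as something to account for. Assuming equal SDs and a correlation of 0.3 to 0.8, the change-score test has 11% to 54% more variance than ANCOVA, a loss of about 4 to 14 percentage points of power at 150 per group. The size rests on those assumptions; the direction does not rest on the value of rho. The gain matters most for the immune indicators, because they carry the second primary objective. The primary intubation analysis and the sample size of 300 are untouched.

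**What to change.** In the Statistical analysis section, and in the analysis plan that is to follow it, replace Student's t test for every continuous outcome with a baseline measurement by ANCOVA: post-treatment value as the response, with arm, the baseline value of the same variable and centre as terms. Report the adjusted difference between arms with its 95% confidence interval. State for blood gases that the same model applies; this also settles whether the level or the change is analysed, because with baseline in the model both give the same treatment estimate.

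The cost is wording only. No data are needed beyond the baseline and post-treatment values that the change outcomes already require, and the sample size does not change. With nine centres the model has 11 parameters (intercept, arm, baseline, eight centre terms) against 2 for the t test, so with 300 patients the residual degrees of freedom go from 298 to 289, which is negligible. The change should be fixed before unblinding.

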### Data management

We will apply two data input mediums in this trial. Researchers will promptly fill in the patients’ information in the paper CRF, and will also enter it into the electronic CRF, followed by regular verification by a clinical research associate (CRA). The modifications made by the clinical investigators will be checked promptly, and the feedback will be provided to the investigators and CRA. The CRA is responsible for the verification of the consistency and accuracy of the paper and electronic CRF, and for feedback to the clinical investigators. Moreover, the principal investigator (PI) of each sub-center will confirm and sign the completed CRF. After the blind review meeting, the data management will lock the data, after which, it cannot be modified. The completed paper CRF transfer between investigators, inspectors, and data managers should be documented and maintained appropriately. The medical information on the subjects is confidential, and disclosure to third parties is prohibited except for the name-related data. The PI can access the final dataset; however, the other investigators are forbidden such access.

### Quality control

#### The construction of the research departments

The design and implementation of a multicenter clinical study requires collaboration among several departments. The quality control and quality assurance are undertaken by these departments as follows: ①an expert committee, which comprises clinical physicians, statisticians, and quality control experts who will be responsible for the establishment of the clinical research methodology and resolve the key issues in the implementation of the study; ②an executive committee: the main members are team members of the expert committee. The responsibilities of the executive committee include the development of clinical research trials, selection of the cooperative hospitals, and organization of meetings related to this trial; ③the DSMB: this is an independent team that evaluates the safety outcomes and AEs and then submits a review proposal; ④data management and statistical analysis; ⑤quality control: to monitor and inspect the sub-centers and researchers will be regularly inspected and monitored throughout the process, following the standard protocol.

#### Monitoring and inspection

This trial will undergo normative monitoring and inspection throughout the whole process. The sub-centers will undergo monitoring once every 2 weeks, which includes details on the integrity and informed consent, criteria for inclusion and exclusion and the original data, treatment of AEs and SAEs, storage conditions and records of transfer, release, and destruction of the research medication. Subsequently, the CRA will submit a report. The inspection contents will as follows: the qualifications of the investigators, the operation of the quality control system in the sub-centers, the integrity and normalcy of the informed consent, normative status and authenticity of the original data, and implementation of randomization. Thus, an inspection report will also be submitted.

